**Evaluation of Triclosan suture in obstetrical surgery**

**Study protocol of a randomized controlled single center trial**

**Introduction :**

Surgical site infection (SSI) presents a burden to healthcare with significant morbidity and mortality(1).

SSI increase direct and indirect costs with a significant overall financial burden for health care system(2). In fact, prolonged hospital stays, increasing rate of readmission and reintervention, are associated with SSI(3).

Several risk factors of SSI had been reported, one of these factors is microorganism colonization of suture materials(4). To prevent this risk, triclosan-coated polyglactin sutures were developed. Triclosan is a phenolic antiseptic with a broad spectrum of antibacterial and antifungal properties and low toxicity. In fact, the concentration used to impregnate or suture poses no risk to humans or the environment. There are no reported carcinogenic, mutagenic or teratogenic effects with such concetration(1). Triclosan gained US food and drug administration approval in 2002 to coat suture materials(5).

Effectiveness of Triclosan coated suture in reducing SSIs was demonstrated in several studies and metanalyses(5–7). Despite these broad evidences, the use of Triclosan coated suture has not been evaluated in obstetric surgery especially in countries with high SSIs incidence.

The main of our study is to determinate whether the use of Triclosan coated suture (Vicryl Plus®) influences the rate of SSI after caesarian delivery (CD) compared to similar Vicryl. Secondary objectives are to analyze contributing risk factors and evaluate the cost impact of antimicrobial suture use.

**Hypotheses**

- The use of antibacterial skin sutures reduces the rate of SSI after ceasarian delivery.

-Triclosan coated suture reduce healthcare cost.

**Methodes :**

**Study designe :**

This is a mono-centric prospective controlled randomized trial conducted in the departement of obstetrics and gynecology of Ben Arous hospital-Tunisia.

It is designed as a triple blind parallel-group superiority trial.

Patients candidate to caesarian section will be informed about the study. Informed consent will be signed by each participating patient and a surgeon of the department before the surgery.

**Data collection and management :**

For data collection we will use an anomymos canevas (Appendix 1), containing six sections: SSI risk factors / Admission / Operative procedure / follow up / SSI diagnosis and management / hospital cost.

Data were collected from: Prenatal follow-up records/ Obstetrical records /Surgical reports/Anesthesia reports/Post-operative monitoring records.

The confidentiality of the participants will be maintained at any time.

The following clinical characteristics will be collected : Age, smoking, Body mass index, presence of diabetes, presence of anemia and history of CD.

Risk factors related to the current pregnancy, will be collected : the presence of gestational diabetes (GDM), preeclampsia (PE) as well as the delay of premature rupture of membranes (PROM) if it exists.

The following information will be collected at the time of the operation : the nature of the caesarean section, operating time, operative complication, the Amerian Society of Anasthesiologist (ASA) score, and the use of an unloading drainage system.

During the postoperative visits, signs of surgical site infections will be cheked , the healing time and the quality of the scar at 30 days will also be noted.

In the presence of a SSI we note its nature, in-patient or out-patient management, antibiotic therapy used, local care kits, imaging examination requested, radiological drainage if needed and the frequency of investigation tests performed.

**Outcomes :**

*Primary outcome:* The rate of SSIs within 30 days after surgery.

*Secondary outcomes*: The rate of wound healing complications.

The cost impact of triclosan coated suture use from a hospital perspective.

***Inclusion criteria:***

Will be include in the study, pregnant woman with elective or emergency caesarian delivery.

***Non-inclusion criteria***:

Suspected or confirmed chorioamniotitis \ SARS-COV2 infection. Patients without signed informed consent were not included.

***Exclusion criteria:***

Cases with incomplete follow-up will be exclude from the study.

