***Sample size calculation:***

The rate of SSI after Caesar section in our center was 9% in 2019. Thus, the assumed expected wound infection rates were 2% with coated suture use versus 9% for the control group. On the basis of a two-sided chi2 test for equality of proportions, the study was expected to have 80% power to detect a relative risk reduction of 5%. A total of 296 patients were estimated to be needed, that is 148 in each arm. The G*Power 3.1.9.6 software (Heinrich-Heine University, Dusseldorf, Germany) was used to calculate the sample size.

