***Randomization:***

After delivering a written consent, patients candidate to caesarian section will be assigned randomly by a computer generated list, to closure with polyglactin non coated suture VICRYL (Groupe 1), or with polyglactin coated suture VICRYL Plus (Groupe 2). The randomization will be performed by Random Allocation Software 1.0.0 (Freeware) by M.Saghaei, MD.

The suture materials for each group will be placed in an opaque sealed box (Box 1 for group 1) and (Box 2 for group 2). The only one allowed to fill the boxes is the senior surgeon responsible of this study

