***Follow up:***

Patients will be followed 30 days after surgery. Four visits were programmed after surgery :

**Check-up 1:** Two days after surgery.

**Check-up 2:** 7 days after surgery.

**Check-up 3:** 15 days after surgery.

**Check-up 4:** 30 days after surgery.

In each visit, wound surveillance will be performed by a resident, and if an SSI is suspected the wound will be photographed and the patient will be referred to a senior surgeon to confirm the diagnosis (figure2).

[figure not shown]

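### The exclusion for undefined incomplete follow-up removes randomised women after treatment and, read plainly, can discard SSIs that are already confirmed

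*Protocol*

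**What the plan says.** Under Exclusion criteria the protocol has a single rule: "Cases with incomplete follow-up will be exclude from the study". It defines neither incomplete nor any exception.

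Four other sections bear on how that rule works:

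- **Randomization:** "After delivering a written consent, patients candidate to caesarian section will be assigned randomly by a computer generated list". Allocation therefore precedes all follow-up.
- **Outcomes:** the primary outcome is "The rate of SSIs within 30 days after surgery", a cumulative yes/no outcome.
- **Follow up:** "Patients will be followed 30 days after surgery. Four visits were programmed after surgery". The first visit is "Two days after surgery" and the others are on days 7, 15 and 30. At each visit, "if an SSI is suspected the wound will be photographed and the patient will be referred to a senior surgeon to confirm the diagnosis". An SSI can thus be confirmed well before day 30.
- **Sample size calculation:** "the assumed expected wound infection rates were 2% with coated suture use versus 9% for the control group", with 148 women per arm. No allowance for excluded women is stated.

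No section names an all-randomised analysis set or keeps women with an observed SSI in the analysis.

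**The concern.** The rule is listed with the eligibility criteria, but it can only operate after randomisation and surgery. Whether a woman completes follow-up may depend on how her wound heals, which is what the trial measures. Removing women on that basis means the arms compared are no longer the arms that were randomised.

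The rule also sits badly with the primary outcome. Once an SSI is confirmed, the 30-day outcome is settled whatever visits are later missed. Taken literally, the rule still removes that woman. It removes her from the study, not from one analysis, so the healing and cost outcomes are affected too. The SSI difference is the denominator of the cost per SSI prevented, and SSI cost is part of total cost.

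This is not detail left to a statistical analysis plan. The protocol states the rule and fixes it badly.

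**Working it through.** **Inputs from the protocol:** SSI rates 9% (control) and 2% (coated), two-sided chi-square test, 80% power, 148 per arm. **Assumptions:** two-sided alpha 0.05 (not stated) and all loss percentages below (no attrition figure is given).

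**1. The plan's own figure.** Cohen's h = 2·arcsin(√0.09) − 2·arcsin(√0.02) = 0.3256. Then n = 2·((1.960 + 0.842)/0.3256)² = 148.08 per arm, which matches the stated 148. Exact enumeration of the uncorrected Pearson test at 148 per arm gives 78.9% power.

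**2. Expected events.** 148 × 0.09 = 13.3 and 148 × 0.02 = 3.0, so about 16 SSIs in all.

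**3. Sensitivity to a few excluded events.** Each excluded woman leaves both numerator and denominator. The uncorrected Pearson statistic is (difference in proportions)² / [p̄(1 − p̄)(1/n₁ + 1/n₂)], where p̄ is the pooled proportion.

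| Control | Coated | Pearson p | Fisher p |
|---|---|---|---|
| 13/148 | 3/148 | 0.010 | 0.018 |
| 11/146 (two control SSIs removed) | 3/148 | 0.027 | 0.030 |
| 10/145 (three removed) | 3/148 | 0.043 | 0.0501 |
| 9/144 (four removed) | 3/148 | 0.069 | 0.082 |
| 13/148 | 5/148 | 0.052 | 0.086 |
| 13/148 | 4/147 (one coated SSI removed) | 0.025 | 0.043 |

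First row: p̄ = 16/296 = 0.0541, difference 0.0676, statistic 6.61. Fourth row: p̄ = 12/292 = 0.0411, difference 0.0422, statistic 3.30.

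**4. Loss that depends on SSI equally in both arms.** If a fraction e of women with SSI and a fraction o of the others are excluded, the observed rate is p(1 − e) / [p(1 − e) + (1 − p)(1 − o)]. With e = 30% and o = 10%:

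- Control: 0.063/(0.063 + 0.819) = 7.1%, with 148 × 0.882 = 130.5 women left.
- Coated: 0.014/(0.014 + 0.882) = 1.6%, with 148 × 0.896 = 132.6 women left.
- Risk difference: 7.14 − 1.56 = 5.6 points, against 7.0.
- Odds ratio: (0.02/0.98)/(0.09/0.91) = 0.206, unchanged, because (1 − e)/(1 − o) cancels. The relative risk moves only from 0.222 to 0.219.
- Exact power: about 64% at 130 and 133 women. Exact power is jagged, and rounding 130.5 up to 131 gives 62%. With the same 130 and 133 women and rates still 9% and 2%, power is 75%.

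The range over other assumed pairs, same method:

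| Lost with SSI / without | Observed rates | Risk difference | Exact power |
|---|---|---|---|
| 30% / 10% | 7.1% v 1.6% | 5.6 points | about 64% |
| 20% / 10% | 8.1% v 1.8% | 6.3 points | 69% |
| 10% / 10% | 9.0% v 2.0% | 7.0 points | 74% |
| 0% / 10% | 9.9% v 2.2% | 7.7 points | 79% |

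The last row is also the narrow reading of the rule, in which only women without a known outcome are removed. Confirmed SSIs are kept there, but both rates and the risk difference are overstated.

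**The case against.** A reader might infer that the rule certainly throws away confirmed SSIs. The protocol does not go that far. Incomplete follow-up could mean any missed visit, or only that 30-day SSI status was never established. Under the second meaning a woman with a confirmed SSI could stay in. What stands is that the term is undefined, that its plain reading drops known events, and that even the narrow reading removes randomised women for a reason arising after treatment.

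A reader might also infer that the rule is likely to reverse the trial's significance. The documents do not support that either. At the planning counts, reversal with the Pearson test needs four control SSIs lost and none in the coated arm. With a 30% chance of loss for each of 13 and 3 SSIs, the probability of at least four control and no coated losses is 0.579 × 0.343, about 20%. The equal-loss scenario gives an expected table of about 9/130 against 2/133, still significant (Pearson p = 0.028).

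Nor does equal loss by outcome distort everything. The odds ratio is unchanged, and the type I error stays near 5% (0.049 by enumeration at 130 per arm, both rates 7.1%). Part of the fall in power comes simply from having fewer women, which no analysis rule fully recovers.

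Finally, the direction of loss is unknown. Women with SSI are referred, treated and costed, and may be retained better than others. The design statement, "It is designed as a triple blind parallel-group superiority trial", also makes loss that differs by arm for reasons other than SSI less likely, though it does not rule it out. These points limit the size of the claim. None of them supplies a reason to exclude a woman whose outcome is known.

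**Conclusion.** The point holds as a badly fixed analysis rule on the primary comparison. The protocol excludes randomised women on an undefined post-treatment criterion and, read plainly, includes among them women whose primary outcome is already known.

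The rule can bias the SSI rates, the risk difference and the cost per SSI prevented, in an unknown direction and by an unknown amount. With about 16 events expected, the result is sensitive to a few women. Four one-sided control losses are needed to lose significance at the planning counts, but one coated-suture event is enough near the threshold. Under equal loss by outcome the damage is to absolute rates and power, not to the odds ratio. These figures rest on alpha 0.05, the protocol's planning rates and illustrative loss percentages.

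**What to change.** 1. Delete the exclusion for incomplete follow-up.
2. State that all randomised women are analysed in the arm assigned.
3. Count any SSI confirmed by day 30 as an event, whatever visits are missed afterwards.
4. Treat the primary outcome as missing only for women with no SSI who were last seen before day 30, and report their number by arm.
5. Test the primary result with a simple sensitivity analysis for those women, for example best/worst case or a tipping point. An imputation model with several risk factors would be fragile with about 16 events.
6. Keep the complete-follow-up set as a sensitivity analysis only.
7. Apply the same all-randomised population to the cost comparison, and say how costs after the last contact are handled.

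The cost is a protocol wording change and a little extra analysis. No extra women or visits are needed.

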***Sample size calculation:***

The rate of SSI after Caesar section in our center was 9% in 2019. Thus, the assumed expected wound infection rates were 2% with coated suture use versus 9% for the control group. On the basis of a two-sided chi2 test for equality of proportions, the study was expected to have 80% power to detect a relative risk reduction of 5%. A total of 296 patients were estimated to be needed, that is 148 in each arm. The G*Power 3.1.9.6 software (Heinrich-Heine University, Dusseldorf, Germany) was used to calculate the sample size.

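### The effect tied to the 80% power claim, a 5% relative risk reduction, contradicts the planning rates of 9% and 2%, which imply a 7-point absolute and 78% relative reduction

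*Protocol*

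**What the plan says.** Everything on this point is in one paragraph of the Protocol, under Sample size calculation.

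- Control rate: "The rate of SSI after Caesar section in our center was 9% in 2019".
- Planning rates: "the assumed expected wound infection rates were 2% with coated suture use versus 9% for the control group".
- Test: "On the basis of a two-sided chi2 test for equality of proportions".
- Power and target effect: "the study was expected to have 80% power to detect a relative risk reduction of 5" per cent.
- Result: "A total of 296 patients were estimated to be needed, that is 148 in each arm".

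The primary outcome, under Outcomes, is "The rate of SSIs within 30 days after surgery". The paragraph gives no significance level. It names G*Power as the software but not the routine used. Nowhere else does the protocol mention or explain a 5% effect.

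**The concern.** Two adjacent sentences give two different target effects. The first fixes the two rates. The second attaches the power claim to an effect that those rates do not produce under any reading of 5% as an effect size. Both cannot describe the same calculation.

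The target effect tells a reader what a non-significant primary result can mean. Taken at its word, the power sentence says the trial would probably pick up even a very small benefit, so a null result would look like strong evidence that coated sutures do nothing. If the design is really sized for a reduction of nearly four-fifths, a null result says little about smaller reductions.

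**Working it through.** **Inputs.** Control rate 9%, coated-suture rate 2%, two-sided chi-square test, 80% power and 148 per arm all come from Sample size calculation. Two-sided alpha of 0.05 is an assumption. It gives z = 1.960, with z = 0.842 for 80% power.

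**1. Effect implied by the planning rates.**
- Absolute reduction: 9% − 2% = 7 percentage points.
- Relative risk: 2/9 = 0.22.
- Relative risk reduction: (0.09 − 0.02)/0.09 = 77.8%.

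The stated 5% is too small by a factor of 77.8/5, or about 16.

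**2. Reproducing the plan's 148 per arm.** The arcsine formula is n = 2 × [(z_α/2 + z_β)/h]², with h = 2·arcsin√0.09 − 2·arcsin√0.02 = 0.3256. This gives n = 2 × (2.802/0.3256)² = 148.08 per arm, which matches the stated figure.

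The other two-sided formulas tried for the same rates do not match: 163 unpooled, 166 pooled, and 193 pooled with continuity correction. One-sided versions give 117 (arcsine), 129 (unpooled), 131 (pooled) and 158 (pooled with continuity correction), and also fail. The stated size is therefore tied to 9% versus 2%, and the fault lies in the description of the effect.

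**3. Sample size under each reading of the 5%.** The pooled formula is n = [z_α/2·√(2p̄(1−p̄)) + z_β·√(p₁(1−p₁) + p₂(1−p₂))]² / (p₁−p₂)², where p̄ is the mean of the two rates.

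- Literal 5% relative reduction: the coated rate is 0.95 × 9% = 8.55%. The denominator is 0.0045² and n = 62,054 per arm, about 124,000 in total.
- Five absolute points below 9% (9% versus 4%): the denominator is 0.05² and n = 381 per arm.
- Five absolute points above 2% (7% versus 2%): n = 269 per arm.

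None is near 148.

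**4. Power at 148 per arm.** The exact column enumerates both binomial distributions and applies the uncorrected chi-square test at 0.05. The last column is the normal approximation.

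| True rates | Relative reduction | Exact power | Normal approximation |
|---|---|---|---|
| 9% vs 2% | 77.8% | 78.9% | 75.5% |
| 9% vs 4% | 55.6% | 40.9% | 41.4% |
| 9% vs 8.55% | 5% | 5.0% | 3.4% |

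For a 5% relative reduction, power equals the type I error rate, so the trial cannot tell that effect from none. If the coated suture cut infections from 9% to 4%, the trial would miss it about 59% of the time (1 − 0.409).

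**The case against.** The strongest defence is that this is one mislabelled number. Both planning rates stand in the preceding sentence, the sample size was evidently computed from them, and correcting the label changes nothing in design, test, outcome or enrolment. The 5% may be a significance level that slipped into the wrong place, since alpha is stated nowhere. A null result would in any case be judged on the estimate and its confidence interval, and no decision rule in the protocol depends on 5%.

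Most of this is fair as far as it goes. The slip does not invalidate the 148 or bias the estimate, and the 62,000 per arm shows that the label is wrong rather than measuring damage to the trial. But the protocol does not say that the 5% is alpha. If it is, the sentence still names a wrong effect and the significance level is missing. The error also sits in the very sentence that states what the trial can detect.

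Three narrower points stand:
- The arcsine origin of 148 is an inference from the match; the protocol does not document it.
- Exact chi-square power at 9% versus 2% is slightly under the claimed 80%. At 152 per arm it is still 79.97%.
- The protocol defines no smallest worthwhile effect, so the 4% scenario is an illustration.

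None of these makes the stated effect correct.

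**Conclusion.** The concern holds. The power claim is attached to the wrong effect: the planning rates mean a 7-point absolute and 77.8% relative reduction. At 148 per arm the design has about 79% power for that effect, about 41% for a five-point drop from 9%, and about 5% for the 5% relative reduction that the text names.

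These figures assume two-sided alpha 0.05, a true control rate of 9%, an uncorrected chi-square test and 148 evaluable women in each arm. Fewer evaluable women would lower power further. The contradiction itself rests on none of these assumptions, because it follows from the two printed rates alone.

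**What to change.** In Sample size calculation, replace the 5% relative risk reduction with: an absolute reduction of 7 percentage points, from 9% to 2% (relative risk 0.22, relative risk reduction 78%).

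Add that power is about 41% if the true coated-suture rate is 4%, so a non-significant result would not exclude a smaller benefit.

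In the same edit, it would help to state the significance level and either name the approximation behind 148 or give the power as about 79%.

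The cost is a sentence or two of protocol text, and a design that looks less favourable on paper. No change to the sample size or to trial conduct is proposed.

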***Randomization:***

After delivering a written consent, patients candidate to caesarian section will be assigned randomly by a computer generated list, to closure with polyglactin non coated suture VICRYL (Groupe 1), or with polyglactin coated suture VICRYL Plus (Groupe 2). The randomization will be performed by Random Allocation Software 1.0.0 (Freeware) by M.Saghaei, MD.

The suture materials for each group will be placed in an opaque sealed box (Box 1 for group 1) and (Box 2 for group 2). The only one allowed to fill the boxes is the senior surgeon responsible of this study

***Surgical procedure:***

A perioperative antibiotic prophylaxis will be administered to all patients.

Per operative hair removal will be prescribed.

Pfannenstiel incision will be performed in all cases.

Uterine and aponeurosis closure will be performed with an overlock suture with 1/0 thread.

Gloves will be changed after aponeurosis closure.

Subcutaneous tissue will be sutured with 2/0 thread.

Skin will be closed with intradermic suture with 3\0 thread.

In the operative room, a scrub nurse verifies the randomization list and delivers the suture material crimped after removing the package. Macroscopically it is impossible to distinguish Vicryl from Vicryl plus.

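### A randomisation list read in theatre and two boxes numbered by arm do not secure allocation concealment, and the triple-blind label is left undefined and unprotected

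*Protocol*

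**What the plan says.** Study design labels the trial: "It is designed as a triple blind parallel-group superiority trial". It does not say which three parties are blinded. On consent, the same section says: "Informed consent will be signed by each participating patient and a surgeon of the department before the surgery".

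Randomization sets the order of events: "After delivering a written consent, patients candidate to caesarian section will be assigned randomly by a computer generated list". Group 1 receives uncoated Vicryl and Group 2 Vicryl Plus. The threads are "placed in an opaque sealed box (Box 1 for group 1) and (Box 2 for group 2"). On preparation it adds: "The only one allowed to fill the boxes is the senior surgeon responsible of this study".

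Surgical procedure describes release in theatre: "In the operative room, a scrub nurse verifies the randomization list and delivers the suture material crimped after removing the package". It then gives the basis for masking the operator: "Macroscopically it is impossible to distinguish Vicryl from Vicryl plus".

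Under Follow up, a resident inspects the wound at each visit and refers any suspected infection to a senior surgeon, who confirms the diagnosis.

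**The concern.** Allocation concealment keeps the coming assignments unknown to anyone who could influence who enters the trial and in what order. Blinding keeps the assignment, once made, from those who treat or assess. The protocol describes one arrangement that is meant to serve both, and it has three weak places.

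- **The sequence.** The list itself is consulted in theatre. Nothing says who holds it, who may see it, or that only the current row is visible.
- **The code.** The containers carry the group number, not a patient number, so the number on the box is the treatment.
- **The assessor.** The senior surgeon who fills the boxes knows the code, and the person who confirms infection is described only as a senior surgeon.

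At stake is the comparability of the arms. If knowledge of coming assignments reaches those who recruit or order the cases, the result is selection bias, which no analysis can reliably repair. If knowledge of the arm reaches the person confirming infection, the primary outcome is exposed, because one criterion for deep infection (Diagnosis of SSI) is simply a surgeon's or attending physician's diagnosis.

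This is trial conduct, which the protocol itself fixes, and not something left to a statistical analysis plan.

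**Working it through.** No figure in the protocol measures concealment, so the main check sets the passages side by side.

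**1. Who can see the sequence.** Surgical procedure puts the list in the scrub nurse's hands in the operating room. A reader of an ordinary list can also read the rows below the current one. No section describes sealing by patient, release by a third party, or limits on access. Exposure is therefore documented for the nurse. For the consenting surgeon (Study design) nothing is documented either way: no passage shows that the surgeon sees the list, and none separates recruitment from those who do.

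**2. What the boxes hide.** An opaque box hides the thread. It does not hide the order of assignments, and its number states the group. The code is constant, so identifying it once identifies every woman with that number. If there is a single box per arm, as the wording suggests, each serves about 148 women and cannot stay sealed after first use. If several boxes per arm were meant, the label would still give the arm.

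**3. Who is blinded.**

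| Role | What the protocol supports |
|---|---|
| Patient | Not stated; nothing suggests she is told |
| Operating surgeon | Masked at handover by unwrapped, look-alike thread |
| Scrub nurse | Unblinded: reads the list and removes the package |
| Senior surgeon filling the boxes | Unblinded: knows the code |
| Resident inspecting the wound | Not stated |
| Senior surgeon confirming infection | Not stated; not excluded from being the one who fills the boxes |

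**4. How few events decide the result (illustration only).** Inputs from Sample size calculation: 9% and 2%, 148 per arm, two-sided chi-squared test. No significance level is stated, so 0.05 is assumed.

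Expected infections: 0.09 × 148 = 13.3 and 0.02 × 148 = 3.0, about 16 in all.

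With equal arms, N = 296 women, m = 16 infections and a difference of d infections between arms, the uncorrected statistic is

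χ² = d² / [m(1 − m/N)], with m(1 − m/N) = 16 × (1 − 16/296) = 15.135.

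| Infections, Vicryl vs Vicryl Plus | d | χ² | p |
|---|---|---|---|
| 13 vs 3 | 10 | 100/15.135 = 6.61 | 0.010 |
| 12 vs 4 | 8 | 64/15.135 = 4.23 | 0.040 |
| 11 vs 5 | 6 | 36/15.135 = 2.38 | 0.12 |

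One infection changing arm leaves the result below 0.05; two take it above. The table keeps arm sizes and total infections fixed, so it supposes that the women moved would have been infected with either suture.

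**The case against.** The strongest reply is that the protocol does more than a quick reading suggests. Assignment follows written consent. No passage gives the scrub nurse a part in eligibility, consent, case order or outcome assessment. Operator masking is described, since the thread arrives unwrapped and the two products are said to look alike. An unblinded dispenser does not by herself unblind the patient, the operator or the assessor.

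Most of this stands, and it rules out three stronger readings.

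- A reader might infer that recruiters know the next assignment. The documents do not say so. The nurse's knowledge would have to reach the consenting surgeon, which is plausible within one department but not stated. Equally, taking consent first protects nothing if the list has already been seen.
- A reader might infer that triple blinding fails. That is not shown. The operator's masking is a real safeguard, and no passage says operators see the box numbers. The supportable statement is that the blinding is undefined and unprotected.
- A reader might infer that the surgical team could vary care by arm. The protocol fixes glove change and antibiotic prophylaxis for all patients, so neither supports that inference.

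It can also be said that the p-values show only the fragility of any trial with about 16 events. That is correct; they are not evidence of bias.

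The reply does not meet the central point. Look-alike thread concerns blinding after assignment. It does not hide a readable sequence or a container labelled with the arm.

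**Conclusion.** The point holds as a defect in the procedure. Followed exactly, the protocol leaves both the sequence and the arm code unprotected, so allocation concealment is not secured. Triple blinding is claimed without naming its parties. At least two people know allocations or the code, and one of them may be the person who confirms the primary outcome.

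No size of bias can be derived, and none is claimed; the direction could be either. The table shows only that, at the planned rates and an assumed 0.05 level, two infections out of about 16 separate a significant result from a non-significant one.

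The conclusion assumes that the list is an ordinary one showing more than the current row, and that no unwritten access rule exists. The figure under Follow up and the data form in Appendix 1 are not in the text read here. If either sets out list custody or blinded roles, that part of the point would narrow. The sample size is unaffected.

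This should be corrected before enrolment, because a failure of concealment cannot be put right afterwards.

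**What to change.** - **Packs.** Replace the two group boxes and the theatre list with sequentially numbered, identical, opaque sealed packs, one per woman, each holding all the threads assigned to her. The outside carries the number only.
- **Preparation.** Have the packs made up from the list by someone who does not recruit, operate or assess, for example the hospital pharmacy, which already supplies the threads (Ethical considerations).
- **Custody.** Keep the list with that person and out of theatre, and state this in Randomization.
- **Release.** Assign the next number only after consent, record it on the data form, and open the pack in theatre. The nurse will still learn that one woman's arm on unwrapping, but not the next woman's. Keep the practice of handing over unwrapped thread.
- **Assessment.** State that nobody who knows the allocation may confirm infection, including whoever prepares the packs.
- **Label.** Name the blinded roles (patient, operating surgeon, resident, confirming surgeon), or drop the term triple blind.

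The cost is the time to prepare about 296 packs, each holding the three thread sizes listed in Surgical procedure, and enough packs to hand for emergency cases. Whether the pharmacy can absorb this is not stated and should be confirmed. The number of patients, eligibility, surgery and visits do not change.
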